#### Client exit interviews

The survey will be powered to provide estimates of clients exit among females 15–19 years of age at the ward level, who will have received ASRH services from health facilities and outreaches. For the purposes of sample size computation, we shall assume a satisfaction level with services of 50% given the lack of a priori indicators in the two counties. The assumed 50% prevalence proportion will give the maximum sample size and any satisfaction level above or below 50% will be overpowered, implying that there will be more precision in the estimates for any other levels of satisfaction. Powering the sample to detect a 15-percentage point difference between the two arms at 85% power, a 95% confidence interval, and a design effect of 1.5, will require a base sample size of 154 in each arm. After accounting for a 20% non-response and incomplete questionnaires, the sample size at recruitment will be 185 per arm in each county. The combined sample size will be 372 respondents at baseline and endline in the two counties, thus a total of 744 (372 baseline and 372 endline). In each of the sub-county where the study will be implemented, the sample size will be allocated proportionate to the number of health facilities and outreaches available.

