### Study design

This will be an 18-month mixed method, quasi-experimental study designed to evaluate the ASRH program’s interventions on the effectiveness of the combined model to improve utilization of ASRH services. Using a qualitative design, data will be collected through focus group discussions (FGDs), in-depth interviews, and key informant interviews. The participants will be purposively selected. Further, we will use exit interviews to study satisfaction among males and females 15–19 years of age who have received ASRH services from health facilities and outreaches (quantitative design). A quasi-experimental design with intervention and control groups will be employed, using a quantitative design to evaluate the effectiveness of the intervention on utilization of ASRH services.

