### Study population

Participants for the qualitative phase of the study will be drawn among adolescents, community members, teachers, healthcare workers, and county health managers in the two counties in the intervention area only, as the findings will be used to shape the intervention. Study participants for the quantitative phase of the study will be adolescents aged 15–19 years. The client exit interviews will target boys and girls aged 15–19 years, who have received any ASRH service at a facility or outreach point. The household survey will target girls aged 15–19 years old who haven’t had their first birth. This is because the unit of measure will be utilization of ASRH services, specifically the use of FP services for primary prevention of pregnancy.

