### Study eligibility criteria

Adolescent boys and girls aged 15–19 years:

• Living, at the time of the survey, in the study sites

• Voluntarily provides informed consent (emancipated minors/adolescents aged 18 and 19 years)

• Voluntarily provides assent coupled with parental permission for minors

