#### Phase 1: formative assessment

A qualitative cross-sectional study design will be utilized for the formative assessment to establish the barriers, preferences, and experiences of adolescents while seeking and using ASRH only. In addition, a pre-intervention and post-intervention client exit interviews will be conducted with both boys and girls receiving ASRH services in health facilities and outreach camps in the intervention and control arms. The aim of the client exit interview will be to establish the quality of ASRH services offered at facilities and outreach points. Information gathered in both formative assessments will be used to develop interventions that will improve access to and quality of ASRH services.

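### The client exit survey is powered for females but takes boys and girls into one undivided sample, so the stated female precision and power are not delivered at the planned size

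*Protocol article*

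**What the plan says.** The protocol article describes the exit survey's population in several places, and they disagree.

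- *Client exit interviews* (the sample size section): "The survey will be powered to provide estimates of clients exit among females", aged 15–19 and by ward.
- *Study design*: "we will use exit interviews to study satisfaction among males and females 15–19 years of age".
- *Study population*: "The client exit interviews will target boys and girls aged 15–19 years, who have received any ASRH service at a facility or outreach point".
- *Phase 1: formative assessment*: "client exit interviews will be conducted with both boys and girls receiving ASRH services in health facilities and outreach camps", in both arms.
- *Study eligibility criteria*, written for the study as a whole: "Adolescent boys and girls aged 15–19 years".

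The sample size section assumes 50% satisfaction, a 15-point difference between arms, 85% power, 95% confidence and a design effect of 1.5. It gives 154 per arm as the base, 185 per arm at recruitment, and 372 respondents per round (744 over baseline and endline). Within sub-counties the number is shared out by the count of facilities and outreaches. No part of it is set aside for either sex.

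**The concern.** The conflict does not look like loose wording. *Study population* treats the two surveys in adjoining sentences and gives boys and girls to the exit interviews and girls alone to the household survey. Boys are evidently meant to be interviewed at exit, yet the number is tied to females.

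Because the total is fixed, each boy interviewed takes a place that the calculation counts as a girl. The stated female precision and power hold only if no boys are interviewed, and three other sections rule that out.

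There is also a lesser consequence for the comparison of arms. The package targets both sexes, and Table 2 marks community and school delivery for the intervention group only. The male share among exit clients could therefore change in one arm between rounds. A pooled comparison would then mix a change in who was interviewed with a change in satisfaction.

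**Working it through.** **Inputs from the document.** Base n = 154 per arm; satisfaction 50%; difference 15 points; power 85%; 95% confidence, read as two-sided 5%; design effect (DEFF) 1.5.

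**Input not in the document.** The male share of exit clients, m. It is assumed here to be 20%, 30% or 50%.

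**1. The plan's own figure.** The usual formula for 50% against 65% is

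n = [z₁√(2p̄q̄) + z₂√(p₁q₁ + p₂q₂)]² / 0.15², with p̄ = 0.575.

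- Two-sided: 194 per arm, and 194 × 1.5 = 291 with the design effect.
- One-sided without the design effect: 155, which is close to 154.

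So 154 does not follow from the inputs as stated. The recruitment figure is 154 × 1.2 = 184.8, rounded to 185. The section assigns 185 to each arm in each county, which would make 185 × 4 = 740 per round, not 372. These are separate problems. I take 154 as given because the loss from counting boys is proportional whichever number is finally used.

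**2. Girls left in the sample.** Girls per arm = 154 × (1 − m).

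**3. Precision among girls.** Half-width = 1.96 × √(0.25 × 1.5 / girls), using the unrounded number of girls.

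**4. Power for 15 points among girls.** Power = Φ{[0.15√n − z₁√(2p̄q̄)] / √(p₁q₁ + p₂q₂)}. It is shown on the stated basis (two-sided, n = girls / 1.5) and on the only two-arm basis found that gives about 154 (one-sided, no design effect).

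| Male share (assumed) | Girls per arm | 95% half-width, points | Power, two-sided, DEFF 1.5 | Power, one-sided, no DEFF |
|---|---|---|---|---|
| 0% | 154 | 9.7 | 59% | 85% |
| 20% | 123.2 | 10.8 | 49% | 77% |
| 30% | 107.8 | 11.6 | 44% | 72% |
| 50% | 77 | 13.7 | 33% | 60% |

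**5. Recruits needed to keep 185 girls per arm.** 185 / (1 − m) gives 232, 265 or 370 per arm at male shares of 20%, 30% or 50%.

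**6. Effect of a change in sex mix.** Shift in a pooled contrast = (gap in satisfaction between the sexes) × (change in male share in one arm only). Neither factor is in the document. With an assumed gap of 15 points and a change of 20 points, the shift is 0.20 × 15 = 3 points. Assuming 10 and 10 gives 1 point, and 20 and 20 gives 4 points, against the 15-point difference targeted.

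**The case against.** The strongest reply is that the reference to females may be the stray word. Nothing in the calculation is specific to girls: 50% is assumed because no prior figure exists, and the other inputs are generic. Three other sections and the eligibility criteria say both sexes. On that reading the number already covers the mixed population, no precision is lost for it, and one sentence needs correcting. This stands, and it is why that correction is among the repairs below. It does not remove the point, because the current text still promises powered estimates for females, which the sample as described does not provide.

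A second reply is that the section promises ward-level estimates while the working above is per arm. This also stands. With 372 recruits over four wards, or 154 completed interviews per arm over two wards, there are about 77 per ward. The half-width is then 13.7 points before any boy is interviewed. If 185 per arm in each county is meant, the base is 154 per ward. The starting precision therefore depends on a conflict still to be resolved; the proportional loss does not.

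Third, a sex quota and analysis by sex may be set out in the full protocol or analysis plan. That is fair, and their absence from the article is not the finding. *Data analysis* also provides for adjustment for changes in composition, although this is written for the household survey comparison.

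Finally, satisfaction is not among the outcomes in *Study outcomes*. The exit interviews serve to describe service quality and inform the intervention, which limits how much rides on the point.

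**Conclusion.** The contradiction is real and stands in current text. The exit survey is stated to be powered for females, while boys and girls enter the same undivided sample. The stated female precision and power are therefore not delivered at the planned size. With assumed male shares of 20% to 50%, the half-width rises from 9.7 points to between 10.8 and 13.7; if few boys attend, the loss is small.

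Three stronger readings are tempting, and the document supports none of them.

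- That no female estimate will be available. A subgroup estimate for girls can still be made from a mixed sample, with wider uncertainty.
- That sex mix will drive the comparison of arms. This needs both a satisfaction gap between the sexes and a change in male share in one arm. Both are assumed, and moderate values give about 1 to 4 points. It is a possible bias of a few points and has not been shown to occur.
- That the main result is at risk. The primary family planning outcome comes from a household survey of girls only and is unaffected.

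**What to change.** Reconcile the sections before recruitment, since girls who were not interviewed cannot be recovered at analysis. Any one of three routes will do.

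1. Restate *Client exit interviews* so that the sample size and power refer to boys and girls together, and drop the claim of powered female estimates. This changes wording only. The cost is a less favourable stated precision for girls.
2. State that the number counts females only, and make boys a separate, descriptive stratum. This needs a count by sex on the recruitment sheet and extra interviews; if boys arrive at 20% of clients, about 232 − 185 = 47 more recruits per arm. Boys' results are descriptive only.
3. Restrict the exit interviews to females in *Study design*, *Study population* and *Phase 1*, and say so in the eligibility criteria. This costs no interviews but gives up boys' views of the services.

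Under routes 1 and 2, adjust for or stratify by sex in the arm-by-round comparison and report the sex mix by arm and round. The per-arm number itself should be settled at the same time.

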### Data analysis

Data from in-depth interviews, FGDs, and key informant interviews will be transcribed, translated, and back translated then entered in qualitative data software (Atlas ti.8). We will then develop a coding frame using a grounded theoretical framework. Independent analysis will be conducted by different analysts and subsequent comparison between the developed coding matrices will be used to develop a reliability factor for the analysis. The trends from the emerging themes will be iteratively developed by repeatedly analyzing data collected at different time points. Verbatim generated alongside the code matrix will be used to support the emerging thematic framework.

Descriptive analysis of quantitative variables will be done using measures of central tendency (mean, median) and measures of dispersion (range, standard deviation), as appropriate. The inter cluster correlation will be computed. We will then conduct an exploratory analysis to compare outcomes by the sociodemographic, cultural, and economic characteristics (age, education, religion, marital status, life skills, wealth quintile, place of residence [urban or rural]) using the Rao-Scott chi-square test to see if there is any association. To determine the relative importance of these factors on the outcomes, generalized estimating equations, univariate, and multivariate logistic regressions will be used to adjust for clustering within the clusters. Results from the regression analysis will be reported as odds ratio and 95% confidence intervals.

For the quasi-experimental design, our hypothesis is that adolescent girls in the intervention study arm will have greater increases in FP utilization and improved knowledge and attitudes than girls in the control arm. We will estimate the intervention effect by subtracting the baseline FP utilization rate from the estimates at endline then calculating the difference between the comparison and intervention sub-counties (the difference-in-difference analysis). The difference-in-differences analysis assumes a common trend in the outcome in both the intervention and comparison area. We will measure potential confounders at baseline and endline and adjust our analysis for any compositional changes over time in these confounders. All statistical analysis will be considered statistically significant for *p*-values less than 0.05.

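### The client exit sample of 154 per arm does not follow from its stated inputs, and 185 per arm in each county contradicts the total of 372 per round

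*Protocol article*

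**What the plan says.** The calculation is in the protocol article under Sampling, Client exit interviews. The reference level is set by assumption: "we shall assume a satisfaction level with services of 50% given the lack of a priori indicators in the two counties". The target is "a 15-percentage point difference between the two arms at 85% power". The text then states that "a 95% confidence interval, and a design effect of 1.5, will require a base sample size of 154 in each arm".

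After a 20% allowance for non-response and incomplete questionnaires, "the sample size at recruitment will be 185 per arm in each county". The next sentence reads: "The combined sample size will be 372 respondents at baseline and endline in the two counties". It then gives 744 as the total over both rounds, 372 in each.

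The same paragraph sizes the survey for females aged 15 to 19. Under Study population, however, "The client exit interviews will target boys and girls aged 15–19 years", and the description of Phase 1 (formative assessment) also has both sexes interviewed.

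**The concern.** There are two separate faults. First, a 15-point difference from 50% at 85% power with a design effect of 1.5 should need far more than 154 per arm, so the stated power may not belong to the stated number. Second, a per-arm, per-county figure must be multiplied by four to give the total for a round, and the stated total is only about twice that figure.

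Field teams cannot tell from the text whether to complete recruitment at 372 or at 740 per round. If 372 is what is done, a finding of no difference in satisfaction would be read as coming from a comparison with 85% power when the true figure is well below that.

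**Working it through.** **Inputs (Sampling, Client exit interviews).** p1 = 0.50; difference 0.15, so p2 = 0.65; power 85% (z = 1.036); design effect 1.5; equal arms; 20% allowance. The 95% confidence interval is taken as a two-sided 5% test (z = 1.960). Data analysis sets significance at p below 0.05 and mentions no one-sided test.

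**1. Attempt to reproduce 154.** With the design effect included, no variant tried gives 154 per arm. The two-sided variants (pooled or unpooled variance, variance fixed at 0.25, continuity correction, rates centred on 50%) range from 286 to 318; the one-sided ones range from 229 to 258. A one-sided 5% test with no design effect gives 152.6 (unpooled) to 154.8 (pooled), but that drops the stated design effect and does not fit a 95% interval.

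**2. Requirement on the stated inputs.**
- Unpooled: n = (1.960 + 1.036)² × (0.25 + 0.2275) / 0.15² = 190.5. Times 1.5 = 285.8, so 286 per arm.
- Pooled variance under the null: n = 193.5, rounded up to 194. Times 1.5 = 291 per arm.

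**3. Power if 154 is the whole arm.**
- Effective n = 154 / 1.5 = 102.7.
- Standard error = √(0.4775 / 102.7) = 0.0682.
- 0.15 / 0.0682 − 1.960 = 0.24, so power is 59.5% (unpooled) or 58.6% (pooled).
- Difference detectable at 85% power from 50%: about 20 points.
- More favourable assumptions do not reach 85%: one-sided with the design effect, 70.4%; two-sided without the design effect, 76.1% (both pooled).

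**4. The 20% allowance.** 154 × 1.2 = 184.8, which is the stated 185. If 20% of 185 are lost, 185 × 0.8 = 148 remain, and power is 56.9 to 57.8%. Keeping 154 after a 20% loss needs 154 / 0.8 = 192.5, so 193. This is a minor point.

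**5. The totals.**

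| Reading | Per arm, both counties | Per round | Two rounds |
|---|---|---|---|
| 185 per arm in each county | 370 | 740 | 1,480 |
| Stated totals | 186 | 372 | 744 |

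372 / 4 = 93 per arm per county. Even 2 × 185 is 370, not 372. The household survey paragraph, under Sampling, shows the multiplication done in full: 2 × 264 + 2 × 231 = 990.

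**6. Power under each reading, pooled over counties, design effect 1.5.**
- 372 per round: about 148 to 154 analysed per arm, power about 57 to 59%.
- 740 per round: 2 × 148 = 296 to 2 × 154 = 308 analysed per arm. Power is 85.7 to 86.2% at 296 and 87.0 to 87.5% at 308.

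**7. Sex.** On the 740 reading, 308 analysed per arm leaves a margin of 308 − 291 = 17 to 308 − 286 = 22 over the requirement. If boys are counted within the number, 85% power for females is lost once they exceed about 6% of respondents (17/308 = 5.5%; 22/308 = 7.1%).

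**The case against.** The best defence is that 154 is a per-county share. The target is worded as a difference between the two arms. Unlike the household survey paragraph, it does not add that the difference is to be detected in each county. If 185 is recruited per arm in each county and the counties are pooled, 296 to 308 are analysed per arm and the stated 85% is met. This stands, and it limits the point. A reader might infer that the 85% claim fails however the paragraph is read; the documents do not support that. The defence has a price, though: it needs 740 per round, so the stated 372 and 744 would be wrong.

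Three other stronger readings also go too far.
- A reader might conclude that the authors used a one-sided test and forgot the design effect. The numerical match is close, but half of a pooled two-sided requirement (about 143 to 146) is also not far from 154. The source of the figure cannot be established.
- A reader might judge the survey on a test within each county. The paragraph speaks of ward-level estimates, but its power target is the difference between arms.
- A reader might judge it on a difference-in-differences between baseline and endline. The article applies that analysis to the household survey, and the power claim here is for a between-arm difference.

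On sex, the paragraph sizes females only and does not say that boys count within 185 or 372. The mismatch with Study population is real, but its effect on power is conditional.

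Finally, satisfaction is not the primary outcome, is not in the table of study outcomes and is not in the stated hypothesis. That lowers the weight of the point but does not remove the error.

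**Conclusion.** The point holds in this form. On the stated inputs about 286 to 291 completed interviews per arm are needed, so 154 does not follow if it is the whole arm; it then gives about 59% power. Separately, the per-county recruitment figure and the stated totals differ by a factor of about two and cannot both be right. The 85% claim is true on one reading only: 740 per round, compared between arms after pooling the counties. At the stated 372 it is about 57 to 59%.

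These figures assume 50% against 65%, a two-sided 5% test, equal arms and a design effect of 1.5 that also applies after pooling. This is a supporting survey of service quality, so the error is less serious than one in the sizing of the primary outcome.

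**What to change.** In Client exit interviews, state one total per round and say whether 185 is per arm overall or per arm per county.

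- **If 372 per round is kept:** replace the claim of 85% power for 15 points with about 57 to 59% power for 15 points, or about 20 points at 85% power, and remove the words that make 185 a per-county figure. No extra interviews.
- **If 740 per round is intended:** correct 372 and 744 to 740 and 1,480, state that 154 is per arm per county, and state that the 85% applies to the comparison pooled over counties. Against the printed totals this is 740 − 372 = 368 more interviews per round, or 736 over both.

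In either case, say whether the number covers females only or boys and girls, and align Study population and Phase 1 with it. If boys count within the number, give the power for females at the expected number of females. Apart from interviews under the second option, the cost is a few restated figures.

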#### Quasi-experimental design

We will conduct a cross-sectional household survey to collect quantitative data to measure knowledge, attitudes, practices, and uptake of ASRH services. The indicator used to compute the sample size was the FP services utilization rate among adolescents aged 15–19 years, using the most current data from the study areas obtained from the Kenya health information system. The FP utilization for both groups was computed and the lowest prevalence of the two was used in computing the sample size to guarantee the maximum possible sample size. An intra-class correlation of 0.03 was assumed resulting in a design effect of 1.87. The study is powered to detect a 15-percentage point difference between the two groups in each county, 95% confidence interval, with power of 80%. Furthermore, we account for a 10% loss due to possible non-responses and incomplete data. Using the parameters described, the sample size was determined to be 264 per arm (total 528) and 231 per arm (total 462) per arm in Kisumu and Kakamega counties, respectively, at each data collection period. A sample size of 990 participants will therefore be interviewed at baseline, and a similar number at endline. Community units are made up of villages, which, for the purpose of sampling, will be “cluster units.” Since the total number of units in each cluster unit and ward is known, villages will be randomly selected; eight villages in Kobura ward and eight from Kajulu ward in Kisumu County. In Kakamega, seven villages in Kholera ward and seven villages in Bunyala West ward. The sample size will be equally distributed among the selected villages in each ward. Households will be selected through systematic random sampling at an interval of 100–200 m from a particular landmark, until the required sample size is achieved for each ward. In households with multiple adolescents, the Kish method will be used to randomly select one individual from each household [10].

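### Household survey: sizing on the lower of two low FP utilization rates gives the smaller sample, not the guaranteed maximum that the protocol claims

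*Protocol article*

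**What the plan says.** The subsection Quasi-experimental design, under Sampling, bases the household survey on the FP utilization rate in 15–19-year-olds, taken "using the most current data from the study areas obtained from the Kenya health information system". A rate was computed for each group, and "the lowest prevalence of the two was used in computing the sample size to guarantee the maximum possible sample size". Neither rate is printed.

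The other inputs are stated:

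- Effect: "The study is powered to detect a 15-percentage point difference between the two groups in each county".
- Error rates: "95% confidence interval, with power of 80" percent.
- Clustering: "An intra-class correlation of 0.03 was assumed resulting in a design effect of 1.87".
- Attrition: "we account for a 10% loss due to possible non-responses and incomplete data".
- Result: "the sample size was determined to be 264 per arm (total 528) and 231 per arm (total 462") for Kisumu and Kakamega respectively, at each survey round.

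The section on study unit inclusion criteria and selection describes the intervention and comparison wards as alike in having low FP utilization. For the exit survey, which also targets a 15-point difference, the subsection Client exit interviews takes a different view of what maximises the sample: "The assumed 50% prevalence proportion will give the maximum sample size".

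**The concern.** With a fixed absolute difference, the required sample depends on the binomial variances of the two arms, and these grow as the rates approach 50%. When both candidate baselines are low, the lower one has the smaller variance and needs fewer participants. The protocol asserts the reverse and calls it a guarantee.

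The primary-outcome sample is therefore presented as the worst case of the two inputs when it is the more favourable one. If the true rate is nearer the higher input, power is below the stated 80%, and a null result would be read as better powered than it was.

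**Working it through.** **Inputs.** From Quasi-experimental design: difference 0.15, power 80%, design effect 1.87, 10% loss, equal arms. I take the 95% confidence interval as two-sided alpha 0.05. The baseline p is not stated and has to be solved for.

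**Formulas.** With q = p + 0.15, p̄ = (p + q)/2 and V(p) = p(1−p) + q(1−q):

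- pooled: n = [1.960·√(2p̄(1−p̄)) + 0.842·√V]² / 0.0225
- unpooled: n = (1.960 + 0.842)²·V / 0.0225
- recruited per arm = n × 1.87 × 1.10

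**Step 1: the plan's own figures.** Removing the inflation gives 264/(1.87 × 1.10) = 128.3 and 231/(1.87 × 1.10) = 112.3.

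- Kisumu, pooled, p = 17%: V = 0.1411 + 0.2176 = 0.3587, n = 127.9, recruited 263.
- Kakamega, pooled, p = 13%: n = 112.5, recruited 231.

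Over the two-sided variants (pooled, unpooled, continuity-corrected; loss as ×1.10 or ÷0.90) the implied baseline is 13–18% for Kisumu and 10–14% for Kakamega. One-sided, it is about 30% and 21–22%. Each equation also has a high solution (about 67–75% two-sided, 55–64% one-sided), which does not fit wards described as low-utilization.

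**Step 2: which of two rates gives the larger n.** Expanding, V(p) = 0.1275 + 1.7p − 2p², which peaks at p = 0.425. For rates a < b:

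V(a) − V(b) = (a − b)·[1.7 − 2(a + b)]

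This is positive only if a + b > 0.85. The pooled term is symmetric about the same point, so the same rule holds. With a lower rate near 17% or 13%, the other group's rate would have to exceed about 68% or 72% for the protocol's sentence to be true. For a 15-point decrease the peak moves to 57.5%, and the lower of two low rates still gives the smaller n.

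**Step 3: possible size.** The higher rates are unknown, so the gaps below are assumptions (pooled formula, ×1.87 ×1.10).

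| Gap between the two rates | Kisumu, lower rate 17% | Kakamega, lower rate 13% |
|---|---|---|
| 0 | 263 | 231 |
| 2 points | 277 | 248 |
| 5 points | 296 | 270 |
| 10 points | 322 | 302 |

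The ceiling, at p = 42.5%, is about 356 per arm.

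**Step 4: power of 264 per arm, one survey round.** Effective n = 128.3; power = Φ(0.15/√(V/128.3) − 1.960), unpooled.

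| Assumed baseline | V | Φ argument | Power |
|---|---|---|---|
| 17.9% | 0.3677 | 0.842 | 80% |
| 20% | 0.3875 | 0.770 | 78% |
| 25% | 0.4275 | 0.639 | 74% |
| 30% | 0.4575 | 0.552 | 71% |

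The pooled version is about one point lower on each row. The same calculation for Kakamega's 231 (effective n = 112.3) gives about 79% at 14%, 68% at 25% and 65% at 30%.

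**The case against.** The best defence of the sentence is that a lower baseline does need a larger sample when the effect is a fixed relative change. That cannot apply here, because the effect is stated in percentage points.

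The objections to making more of the point are stronger, and they stand:

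- **Size.** Neither rate is printed, and the wards were chosen to be alike in low utilization, so the two rates may be close. A 2-point gap costs about 5% more participants in Kisumu (277 against 263). Nothing in the document places the higher rate at 25% or 30%.
- **Back-solved baselines.** These are ranges that depend on the formula. Also, 264 = 8 × 30 × 1.10 and 231 = 7 × 30 × 1.10, which match eight and seven villages at the 30 per cluster that the design effect implies (1 + 29 × 0.03 = 1.87). If the figures were rounded up to whole villages, the implied baselines are lower still. The direction is unchanged, but the size is even less certain.
- **Exit-survey statement.** It conflicts with the household-survey rationale, but it is not an exact benchmark: for a 15-point increase the peak is at 42.5%, not 50%.
- **Contrast.** The figures above are for one survey round. The primary analysis is a difference-in-differences, for which they are not the power.

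A reader might infer that 264 and 231 are wrong, or that the study is badly underpowered. The document supports neither: both figures are consistent with the stated inputs at some low baseline. Nor is it true that any lower rate under about 42% gives the smaller sample: with 40% and 50% the sum is 90%, and the lower rate gives the larger n. The condition is on the sum of the two rates.

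**Conclusion.** The stated rationale is wrong. For a fixed 15-point absolute increase from low baselines, taking the lower rate gives the smaller of the two candidate samples, so the claimed guarantee is false. The direction is secure: every two-sided and one-sided back-solution consistent with low utilization lies well below 42.5%, and the comparison rate that would rescue the sentence is implausible for wards matched on low use.

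The size is not known. It depends on two unprinted rates, and the requirements and power figures above are illustrations under assumed gaps and baselines. A further rise in the rate from restricting the outcome to sexually active girls is a separate denominator question and is not counted here. The point should be fixed, but it does not by itself invalidate the sample size.

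**What to change.** In Quasi-experimental design, under Sampling:

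1. Delete the closing clause that promises the largest possible sample.
2. Print both groups' FP utilization rates for each county.
3. State that the conservative choice is the rate that gives the larger n, here the higher one.
4. Restate the power of 264 and 231 per arm at that rate, labelled as power for a single-round two-arm contrast so that it is not read as power for the difference-in-differences.

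The cost is one rewritten sentence, a few printed figures and a somewhat less favourable stated power. The sample itself need not change unless the restated power is judged too low.
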